# Impact of perinatal environmental health education intervention on exposure to endocrine disruptors during pregnancy—PREVED study: study protocol for a randomized controlled trial

**DOI:** 10.1186/s13063-021-05813-5

**Published:** 2021-12-04

**Keywords:** Endocrine disruptors, Maternal exposure, Pregnancy, Environmental health, Intervention research, Randomized controlled trial

## Abstract

**Background:**

The suspected or actual effects on health of endocrine-disrupting chemicals (EDC) and their ubiquitous presence in everyday life justify the implementation of health promotion interventions. These interventions should ideally be applied during critical windows like pregnancy. Perinatal environmental health education interventions may help to reduce EDC exposure during pregnancy.

**Methods/design:**

PREVED (Pregnancy, PreVention, Endocrine Disruptors) is an open-label randomized controlled trial assessing the impact of environmental health education intervention on EDC exposure during pregnancy. Inclusion, consent, and randomization take place during the first trimester. The participants are randomly allocated into three groups: (i) control group (information leaflet on EDCs), (ii) intervention group in neutral location (information leaflet and workshops in a meeting room), and (iii) intervention group in contextualized location (information leaflet and workshops in a real apartment). Workshops are organized between the second and third trimesters of pregnancy. Main outcome is the percentage of participants who reported consuming manufactured/industrial food. Secondary outcomes are as follows: (i) psycho-social dimensions, (ii) EDC concentrations in urine, (iii) EDC concentration in colostrum, and (iv) percentage of participants who reported consuming paraben-free personal care products.

**Discussion:**

PREVED is a ground-breaking intervention research project dedicated to perinatal environmental health education that aims to identify pollutant sources in daily life and to offer accessible and realistic alternative solutions, by promoting the sharing of know-how and experience in a positive and non-alarmist approach.

**Trial registration:**

ClinicalTrials.gov: NCT03233984 (current status: ongoing). Retrospectively registered on 31 July 2017 (https://clinicaltrials.gov/ct2/show/NCT03233984) because when the first participant was enrolled in this non-drug intervention, ClinicalTrials.gov was centered in therapeutic trials.

The World Health Organization Trial Registration Data Set is in Additional file 1.

**Supplementary Information:**

The online version contains supplementary material available at 10.1186/s13063-021-05813-5.

## Background

The in utero period is an important period that conditions health in adult life. Prenatal exposure can disturb fetal and neonatal development [1] and lead to numerous disorders [2–4]. These health consequences are especially underlined by FOAD- (Fetal Origins of Adult Disease) [5], DOHaD- (Developmental Origins of Health and Disease) theories [6, 7], which emphasize the importance of intrauterine environmental exposure in offspring health, and by POHaD-theory (Paternal Origins of Health and Disease), which underlines the role of paternal environment and exposure [8].

The concept of “exposome” initiated in the 2000s is along the same lines. Indeed, exposome includes lifetime exposures from periconceptional period until death [9]. Under this concept, exposures can be classified as [10, 11]:
Internal exposure: combining all endogenous factorsSpecific external exposure: combining exogenous factors such as chemical contaminants, environmental pollutants and lifestyle factorsGeneral external exposure: taking into account a wider environment with social, economic, and psychological factors

Among these exposure factors, endocrine-disrupting chemicals (EDCs) are chemicals and environmental pollutants defined by the World Health Organization (WHO) as “exogenous substances or mixture that alter function(s) of the endocrine system and consequently cause adverse health effects in an intact organism, or its progeny, or (sub)-populations” [12]. EDCs may be synthetic such as parabens (PB) and phthalates found in cosmetics, bisphenol A (BPA) found in plastics, or pesticides such as atrazine or trifluralin found in soil or food. They may also be natural such as hormones or phytoestrogens [13].

Their involvement is confirmed, or at least suspected, in the development of numerous diseases or disorders, especially on reproduction, hormone-dependent cancers [14, 15], and metabolic disorders [16]. This is typically the case of diethylstilbestrol, an estrogen medication which was prescribed for pregnant women in the 1940s [17]. Many decades later, prenatal exposure to diethylstilbestrol was recognized as the cause of many diseases for children exposed in utero, and even for grandchildren who had never been directly exposed [18–20]. In fact, exposure to several EDCs at specific developmental stages called “susceptibility” or “critical windows” such as prenatal and puberty periods causes more pronounced health effects [14, 21, 22].

In 2016, the European Commission made recommendations on prioritizing human epidemiology (follow-up cohorts…), knowledge about exposure (chemical markers, biomarkers…), and effects in wildlife [23], and in its strategic approach, issued in 2018, emphasis was put on prevention interventions, particularly in “critical windows” [24]. Thus, several steps were necessary to take into account EDC exposure [25].

Promotion health interventions should be carried out since the pre/periconceptional period [26], which comprises key moments of exposure sensitization and environmental health promotion [27, 28]. There are numerous recommendations and interventions aimed at improving maternal and infant health, for instance, on nutrition [29–31], iron supplementation [32], physical activity [33], hypertensive disorders [34], oral health [29], or on reduction of environmental tobacco smoke exposure [35, 36]. However, only a few of them concern EDC exposure [37–40].

To our knowledge, there exists no research study focused on perinatal exposure through the prism of environmental health education in France. Our hypothesis was that an extended perinatal environmental health education intervention conducted during pregnancy by promoting the sharing of know-how and experience in a positive and non-alarmist approach would contribute to the reduction of EDC exposure.

The PREVED (Pregnancy, PreVention, Endocrine Disruptors) study aimed to assess the impact of an environmental health education intervention on prenatal exposure to EDCs. The secondary objectives are to assess the impact of the intervention on psycho-social dimensions, EDC concentration in urine and colostrum, and on the choice of personal care products. The EDCs studied are BPA, its chlorinated derivatives, and PB: methyl-, ethyl-, propyl-, and butyl-PB.

## Methods

### Study design

The PREVED study is an ongoing open-label, monocentric, randomized (1:1:1) controlled superiority trial, parallel-designed, three-armed with:
A control group: group (1)An intervention group in neutral location: group (2)An intervention group in contextualized location: group (3)

### Participants and interventions

The PREVED study is conducted in Poitiers (France). Recruitment was held from April 2017 to April 2019. The site of intervention is in an underprivileged and multicultural Poitiers neighborhood with strong associative potential (animation center, young workers’ home and sports center), where women of low socioeconomic and educational status may be particularly exposed to EDCs [41].

According to the allocation group, workshops are performed in two different locations. Group 2’s intervention is performed in a meeting room in the “Animation Centre of the neighborhood,” which is a neutral location. Group 3’s intervention is performed in “*Atelier du 19*,” an apartment dedicated to health/environment education in everyday life [42].

Inclusion and exclusion criteria are detailed in Table 1.

**Table 1 Tab1:** Inclusion and exclusion criteria for the PREVED study

Inclusion criteria	Exclusion criteria
- Pregnant women with declared pregnancy - Speaking French - Being aged 18 years or more - Living in the French department of Vienne and at less than 30 min from Poitiers - Having the intention to give birth in the maternity of the University Hospital, of the clinic “Fief de Grimoire” in Poitiers or in the Hospital of Châtellerault - Having signed a consent form	- Pregnant women expecting twins or more - Having a complicated pregnancy - Not speaking French - Being under 18 years old or under legal protection despite being 18 or more - Being deprived of liberty by judicial or administrative decision - Undergoing psychiatric treatment - Not being affiliated to a social security system - Intending to move out during the next year - Having the intention to give birth in a maternity ward other than the department of Vienne - Being unable to express consent

PREVED study implementation was preceded by an essential step involving pregnant women and professionals. Qualitative and quantitative studies were carried out to describe pregnant women’s knowledge, attitudes, and behaviors towards EDC exposure [43], to estimate their risk perception [44], and to determine environmental health knowledge, attitudes, and practices of prenatal healthcare providers [45]. These results facilitated the design of the intervention and the identification of the aims and outcomes of PREVED study.

Furthermore, the study was preceded by the creation of a “DisProSE Group” steering committee, a consortium of researchers, local actors, and decision-makers who co-built the intervention, initially developed by a mutual insurance company, according to PREVED’s aims and to behavior change techniques (BCT) taxonomy [46].

After complete recruitment, we could analyze the intervention, which involved 12 of the 16 BCTs, in view of diversifying approaches (Table 2).

**Table 2 Tab2:** Behavior change techniques (BCT) used for the intervention of PREVED study

Grouping of BCT taxonomy	Chosen BCT in each BCT group	Example of an intervention
*Goals and planning*	Problem solving	- To identify behaviours that are easy to implement daily to reduce exposure to endocrine disruptors chemicals (EDC) (example: replace plastic with glass)
	Action planning	- To integrate the purchase of primary products into your personal planning and devote time to manufacturing cosmetics at home
*Feedback and monitoring*	Not applicable	- No feedback between the workshops/Only a series of workshops by participant
*Social support*	Not applicable	- Few attendants came to the workshops
*Shaping knowledge*	Training on how to perform the behavior	- To learn to read package labels - To learn to prepare cookies and cosmetics at home
	Behavioral experiments	- To appreciate the changes implemented daily to reduce their exposure to EDCs thanks to the three-time questionnaire which to compare her consumption before and after
*Natural consequences*	Information about health consequences	- To respond to participants' questions about the known effects of EDCs exposure during pregnancy
	Information about social and environmental consequences	- To present the consequences of behaviours aimed at reducing EDCs exposure on the environment (example: waste reduction through homemade products)
*Comparison of behavior*	Demonstration of the behavior	- To teach how to make one’s own cosmetics
*Associations*	Prompts/clues	- To highlight leaflets and documentation at home
*Repetition and substitution*	Behavioral practice/rehearsal	- To integrate the manufacture of cosmetics into your schedule: the recipes offered were inexpensive and easy to integrate into a routine without constraints
	Behavior substitution	- To avoid heating food in plastic dishes with a microwave oven
	Habit formation	- To encourage participants to ventilate the house for 20 minutes/day
	Habit reversal	- To use glass jars and boxes to store food and meal leftovers, instead of plastic packaging
	Generalization of target behavior	- To teach how to make one’s own cosmetics in order to be independent/repeat the manufacture at home
	Graded tasks	- “Change everything” is neither taught nor required to propose simple solutions to reduce exposure to EDC
*Comparison of outcomes*	Credible source	- To use of current data from literature
	Pros and cons	- To explain that using glass packaging instead of plastic is valuable but not without some constraints (heavier, risk of breaking)
	Comparative imagining of future outcomes	- To project yourself at home (eliminating / reducing EDCs sources) in particular to safe your health and your children health
*Reward and threat*	Material reward	- To bring home the products made during the workshops (floor cleaner, cookies, ...): quick practice and experimentation directly after the workshop - To reimburse the travel costs of participants (planned but not implemented)
*Regulation*	Conserving mental resources	- To recall the pleasure of consuming healthy products - To encourage the implementation of even small changes on a daily basis: Choose not-guilty and counterproductive words
*Antecedents*	Adding objects to the environment	- To bring home made products: reusable containers will remind the participants of the value of making their own products and encourage them to continue manufacturing
*Identity*	Framing/reframing	- To rely on a presentation of a positive vision of health - Do not focus on pathologies - To encourage exchanges: sharing of experiences and knowledge is complementary to the information given by the facilitators
	Incompatible beliefs	- To remember that a "Natural Product" is not necessarily a "Safe Product" or a "Healthy Product" - To explain that it is not necessary to go from “all industrial” to “all homemade”: by reading the labels, it is possible to better choose products containing little or no EDCs (number of ingredients, absence of 'additives ...)
*Scheduled consequences*	Not applicable	
*Self-belief*	Verbal persuasion about capability	- To reassure participants: no guilty speech - To highlight simple and accessible solutions to limit EDCs exposure: positive reinforcement
	Focus on past success	- To encourage the sharing of experience and information between participants (example: multiparous participants can advise new parents on "tips and tricks")
*Covert learning*	Not applicable	

No concomitant intervention is prohibited. Women randomized in the control group are told that they are entitled to have the program after the end of the study (1 year after delivery).

The list of pregnant women is obtained through pregnancy declarations, which are centralized in rance by “*Protection Maternelle et Infantile*” (maternal and child protection) or PMI. The investigator sends to eligible women an informative postal mail with a prepaid envelope. Women who wished to participate in PREVED study confirmed their interest by phone or mail.

To improve enrolment, information leaflets are sent to general practitioners and midwives working in the enrolment area. To achieve representative and adequate enrolment, PMI’s midwives were trained to present the PREVED study to pregnant women. Local actors in social centers and the associative sector also assisted in enrolment. The first participant was enrolled on 17 April 2017.

The intervention consisted of a sequence of three workshops held between the second and the third trimesters of pregnancy. It incorporated the results of a previous workshop [43] and aimed to identify pollutant sources in daily life and to offer accessible and pragmatic alternative solutions by promoting the sharing of know-how and experience in a positive and non-alarmist approach. Three themes are addressed (Table 3). Any participant may at any time withdraw from this study and adherence participation is encouraged with adapted meeting.

**Table 3 Tab3:** Detailed workshops for the intervention of PREVED study

	Workshop 1	Workshop 2	Workshop 3
***Theme***	Indoor air quality	Nutrition	Personal care products
***Duration***	2 h	2 h	2 h
***Participants***	10 people: pregnant women ± spouse, friend, or parent	10 people: pregnant women ± spouse, friend, or parent	10 people: pregnant women ± spouse, friend, or parent
***Facilitator***	Medical advisor for indoor environments	Dietician trained in environmental health	Cosmetologist
***Pedagogic objectives***	- To detect and reduce sources of domestic air pollution - To share know-how, experiences, and information on alternatives	- To identify food pollutants - To share know-how, experiences, and information on alternatives	- To identify necessary elements to make healthy choices of personal care products and clothes - To share know-how, experiences, and information on alternatives

The DisProSE group produced an information leaflet providing advice on ways of reducing EDC exposure in relation to the aforementioned themes. This leaflet was designed according to the principles of health literacy to be as accessible and comprehensible as possible [47]. All participants, including group 1, receive it during the first home visit. The only difference between group 2’s workshops and group 3’s workshops is the location of the intervention.

Fig 1. summarizes the conduct of PREVED study.

**Fig. 1 Fig1:**
[figure not shown]
Description of the three groups of the PREVED study

#### Main outcome

Percentage of participants who reported consuming manufactured or industrial food determined through a sociodemographic and consumption questionnaire (Q1) developed by our research team [48] and administered at t0, t + 2 months and t + 14 months.

#### Secondary outcomes

Mean score of psychosocial questionnaire (Q2) developed by our team, whose dimensions are presented in Table 4Urinary concentrations of: BPA, chlorinated derivatives of BPA, methyl-, ethyl-, propyl-, and butyl-PBConcentration in colostrum of: BPA, methyl-, ethyl-, propyl-, and butyl-PBPercentage of participants who reported consuming PB-free personal care products

**Table 4 Tab4:** Dimensions of the psychosocial questionnaire used in PREVED study

Dimension of the psychosocial questionnaire	Origin of corresponding question or questions	Comment
***Self-esteem***	French version of the “Self-esteem scale” [49]	Score ranges from 10 to 40: the lower the score, the lower self-esteem. Items for this score are self-administered
***Perceived health***	Created for the questionnaire	Score ranges from 0 to 100 on a visual analogic scale
***Health care renunciation and risk aversion***	Inspired by French national investigations [50, 51]	Use of visual analogic scales
***Risk perception***	Created for the questionnaire and based on the Perception of Pregnancy Risk Questionnaire [52]	Use of visual analogic scales. A composite and global score of perinatal risk perception related to EDC exposure was created
***Knowledge about endocrine-disrupting chemicals (EDCs):*** routes and sources of exposure, ability to name some EDC’s molecules or families of molecules and definition of an EDC	Created for the questionnaire	A composite score was created. A catalog of photo images illustrates sources of exposure
***Perceived knowledge about EDCs***	Created for the questionnaire	Use of a visual analogic scale
***Expectations for a “healthy baby”***	Based on “the healthy baby concept” [53]	Use of a visual analogic scale and a catalog of photo images
***Trusted person***	Created for the questionnaire	The answer to this question aims to identify the trusted person, who exerts the most influence on the pregnant woman
***Level of concern about five risks related to pregnancy***	Created for the questionnaire	This exploration is meant to establish a hierarchy, with respect to chemical risk concerns. A catalog of photo images is used
***The way the pregnant woman heard about EDCs and, if so, how she experienced the information she received***	Created for the questionnaire	These two parameters explore the role of information provided by the media, professional studies, and relationships (personal, friendly, professional, health professionals)
***Relationship to risk visibility***	Created for the questionnaire	Likert-type response

The planning of the administration of questionnaires and the collection of samples is summarized in Fig 2.

**Fig. 2 Fig2:**
[figure not shown]
Course of the PREVED study

Time schedule of enrolment, intervention, assessments, and visits are detailed in Table 5. They were carried out according to the SPIRIT Guideline (Additional file 2).

**Table 5 Tab5:** SPIRIT flow diagram of schedule of enrolment, interventions, and assessments in PREVED study

	Enrolment	Post-allocation				Close-out	
Timepoint	***Baseline***	***t***_***0***_	***t***_***+1M***_	***t***_***+2M***_	***t***_***+4M***_	***t***_***+14M***_	
		Home visit 1		Home visit 2	Childbirth	Home visit 3	
		Leaflet	Workshops				
**Enrolment:**							
**Eligibility screen**	X						
**Informed consent**	X						
**Allocation**	X						
**Interventions:**							
***Group 1*** *Control group*		X					
***Group 2*** *Intervention group in neutral location*		X	X				
***Group3*** *Intervention group in contextualized location*		X	X				
**ASSESSMENTS:**							
***Q1*** *Sociodemographic questionnaire + consumption habits*		X		X		X	
***Q2*** *Psychosocial questionnaire*		X		X		X	
***Collection of urine samples***		X		X	X	X	
***Colostrum samples***					X		

### Sample size

According to the results of the EDDS (Endocrine Disruptors Deux-Sèvres) cohort study, 83% of French women consumed canned food [48]. Thus, we calculated the number of participants based on the primary outcome measure (consumption measure) using a two-sided paired sample *t* test with 0.05 level of significance two-way design and *β* = 0.20. Our hypothesis was that the contextualized intervention would decrease this percentage to 60%, representing a decrease of 23 points, and 58 participants were required for each group. We expected 20% of lost to follow-up participants; consequently, 70 participants are required for each group, out of a total of 210 pregnant women to be included in our study. This number was increased to 273 persons due to significant colostrum loss in an amendment submitted to the Committee for Personal Protection who approved the first protocol (protocol version 10 approved by the Committee for Personal Protection on 15 June 2018).

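### Sample size: the named paired t test does not match the calculation that gives 58 per group, and a 20% loss needs 73 per group, not 70

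*Protocol article*

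**What the plan says.** The Sample size section of the protocol article starts from a cohort figure, "83% of French women consumed canned food", and assumes that the contextualized intervention lowers it to 60%, a fall of 23 points. On the method it says "we calculated the number of participants based on the primary outcome measure (consumption measure) using a two-sided paired sample" t test, with a 0.05 "level of significance two-way design and *β* = 0.20". The result is 58 per group. It continues: "We expected 20% of lost to follow-up participants; consequently, 70 participants are required for each group", giving 210 in total. It then reports: "This number was increased to 273 persons due to significant colostrum loss in an amendment", and gives the protocol version and approval date for that change.

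Three other places bear on this. Main outcome defines the measure as a percentage of participants, so each woman contributes a yes or a no. Study design describes a randomised 1:1:1 parallel superiority trial with three arms. Data collection, management, and analysis says the main outcome is compared between home visits 1 and 2.

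**The concern.** A paired t test compares two measurements on the same person. Sizing it needs the SD of the within-person difference, or for a yes/no outcome the correlation or discordant proportion; the section gives none of these. A randomised parallel trial is normally sized on the difference between arms, which needs only the two percentages. As written, the reader cannot tell whether 58 powers a before-after change within one arm or a difference between arms. Only the second uses the randomisation.

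The allowance for loss is a separate matter. If 58 evaluable women per group are needed and 20% are lost, the enrolled number times 0.8 must be at least 58. Seventy does not meet that condition.

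At stake is whether 58, 70, 210 and 80% power fit together and describe the comparison the trial will make.

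**Working it through.** **Inputs, all from the Sample size section:** p1 = 0.83, p2 = 0.60, difference 0.23, two-sided alpha 0.05 (z = 1.960), power 0.80 (z = 0.842), 58 evaluable per group, 20% loss, 70 per group, 210 in total, later 273. The 1:1:1 ratio is from Study design.

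**1. Reproducing 58 with two independent proportions.**
- Sum of variances: 0.83 x 0.17 + 0.60 x 0.40 = 0.1411 + 0.2400 = 0.3811.
- Unpooled: n = (1.960 + 0.842)² x 0.3811 / 0.23² = 56.5, so 57.
- Pooled: mean proportion 0.715; n = [1.960 x √(2 x 0.715 x 0.285) + 0.842 x √0.3811]² / 0.23² = 59.3, so 60.
- Two-sample t on 0/1 data: 57.5, so 58. Arcsine: 58.2, so 59.

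All four lie within 2 of 58. The continuity-corrected version (68) and the one-sided pooled version (47) do not.

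**2. The test actually named.** For a paired t test on yes/no answers with within-woman correlation r, the variance of the difference is 0.3811 − 2r√(0.1411 x 0.2400) = 0.3811 − 0.3680r. The article gives no r, so a range is assumed:

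| r (assumed) | SD of difference | n, paired t |
|---|---|---|
| 0 | 0.617 | 58.5 (59) |
| 0.1 | 0.587 | 53.0 (54) |
| 0.3 | 0.520 | 42.1 (43) |
| 0.5 | 0.444 | 31.2 (32) |

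Exactly 58 corresponds to r of about 0.01. The largest r these two percentages allow is (0.60 − 0.83 x 0.60)/0.184 = 0.55, so 0.5 is close to the extreme. The named test therefore gives 58 only when pairing brings no gain.

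**3. The allowance for loss.**
- The article's route: 58 x 1.2 = 69.6, so 70; 3 x 70 = 210. Both stated figures are reproduced.
- Check: 70 x 0.8 = 56 evaluable, which is 2 short of 58.
- Correct: 58 / 0.8 = 72.5, so 73; 3 x 73 = 219.

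**4. Effect on power (independent proportions, 83% v 60%).**

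| Evaluable per arm | Pooled | Unpooled |
|---|---|---|
| 56 (70 less 20%) | 77.7% | 79.6% |
| 58 (as required) | 79.1% | 81.0% |
| 73 (91 less 20%) | 87.6% | 88.9% |

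The slip costs 79.1 − 77.7 = 1.4 points pooled, or 81.0 − 79.6 = 1.4 unpooled.

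**5. The amended total.** 273 / 3 = 91 per arm if 1:1:1 was kept, and 91 x 0.8 = 72.8. With 72 rather than 73 evaluable the pooled power is 87.2%. The range is therefore about 87-89%.

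**The case against.** The strongest reply is that nothing of consequence is wrong. The figure of 58 is sound for the two percentages given, and a paired t test at zero correlation gives 58.5, so it cannot be said that the named test is unable to produce 58. The analysis section also compares home visits 1 and 2, so paired wording is not out of nowhere. The inflation slip is three women per group, and 91 per arm is already above 73. All of this stands, and it limits the point to a misnamed test and one wrong multiplication. It does not remove either: no correlation or SD is stated to support a paired calculation, and 70 and 210 do not follow from 58 and 20% loss.

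A reader might infer more in four ways that the article does not support.
- **That the trial is underpowered.** On its own inputs, 273 gives more than the planned 80%.
- **That 273 is unjustified.** The article gives the reason, the approval and the protocol version. The calculation may stand in the amended full protocol, which is not shown, and enrolling more women for colostrum cannot reduce power for the main outcome.
- **That 58 should become 60, or 75 per arm after loss.** That only prefers the pooled formula; 57 to 60 are all acceptable.
- **That power collapses because controls also improve.** Controls do receive the leaflet, and Table 2 counts the repeated questionnaire as a behaviour change technique ("thanks to the three-time questionnaire which to compare her consumption before and after"). With 73 per arm and 60% in the contextualized arm, power would be 65.5% if controls fell to 78% and 49.0% at 75%. Neither control rate appears in the article; both are illustrative assumptions and show no error in the calculation.

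**Conclusion.** Two statements in the Sample size section are wrong and should be corrected. The test named is not the one that naturally yields 58 for a yes/no outcome in parallel arms, and its extra input is missing. The allowance for 20% loss should give 73 per group and 219 in total. The practical size is small: 2 evaluable women per group and about 1.4 points of power under the replaced target of 210, and no shortfall at 273. What is affected is whether a reader can tell which comparison the trial was sized for.

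This rests on taking 83%, 60% and 20% loss as stated, and on 1:1:1 allocation having been kept at 273. The correlations in the paired check are assumed.

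**What to change.** In the Sample size section, or wherever the sample size is next reported:
1. Replace the paired t test with a two-sided comparison of two independent proportions between randomised arms (83% v 60%, alpha 0.05, 80% power), and name the arms and the formula that gave 58. If a within-woman comparison really was intended, give the correlation or discordant proportion used.
2. Correct 70 per group and 210 in total to 73 and 219 (58/0.8).
3. State that 273 (91 per arm, about 73 evaluable after 20% loss) gives about 87-89% power for 83% v 60%.
4. Optionally, show power under a lower control rate, labelled as an assumption, since controls also receive the leaflet.

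The cost is wording only. No participants are added and the conduct of the trial does not change.
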